### Eligibility and non‐eligibility

2.2

This study focuses on HFrEF patients who meet the criteria for receiving ICD for primary and secondary prevention of SCD and those who meet the criteria for WCD for primary prevention. Participants must be 20 years of age or older at the time of obtaining consent and provide written consent based on their own free will after receiving sufficient explanation regarding participation in this study. Patients eligible for this study will be basically fulfilled with the criteria of class I or IIa for ICD including sub‐cutaneous ICD (*S*‐*ICD*), and WCD as outlined in the JCS guidelines^1^: (1) patients with coronary artery disease (CAD) (≥40 days after myocardial infarction (MI) and at least 90 days after revascularization) or non‐ischemic cardiomyopathy who have NYHA class II or greater symptoms and an LVEF ≤35% despite optimal medical therapy, irrespective of whether they've experienced NSVT (criteria for primary prevention of SCD), (2) CAD or non‐ischemic cardiomyopathy who have NYHA class II or greater symptoms and an LVEF ≤35% accompanied by ventricular fibrillation (VF) or out‐of‐*hospital* cardiac *arrest* requiring electrical shock, sustained VT or unknown syncope, not due to reversible causes (criteria for secondary prevention of SCD), and (3) patients with LVEF ≤35% and HF symptoms of NYHA class II or III, and within 40 days after the onset of acute MI, and are within 90 days after coronary artery bypass or percutaneous coronary intervention, or within 90 days after the acute onset of HF due to a non‐ischemic etiology (WCD criteria). Therefore, this study will also include the patients who have opted not to receive ICD or WCD based on the patients' preference, including those without any cardiac device or those with CRT‐P. The following patients are excluded from this study: (1) those with a life expectancy of less than 12 months, (2) patients with frequent recurrent VT or VF that cannot be controlled with antiarrhythmic drugs or catheter ablation, (3) severe HF patients classified as NYHA class IV, (4) individuals unable to provide consent for the study, and (5) others judged unsuitable as study subjects by the principal researcher.

In short, the target cases for this study are those aged 20 or older with LVEF ≤35% and NYHA class II or higher HF symptoms despite adequate medical therapy, who do not fall under the exclusion criteria mentioned above.

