### Study schedule

2.3

Patients diagnosed as eligible for ICD or WCD indications will start enrollment in this study when informed consent regarding their medical condition and treatment options is obtained. All items at the time of enrollment and follow‐up in both of patient groups eligible for ICD and WCD indications, are listed in Tables 1 and 2. The brief items include age, gender, height, weight, dairy habits, underlying heart disease, NYHA functional classification, medical history, Clinical Frailty Scale,^22^ medication history including HF treatment, the presence of atrial fibrillation/flutter or NSVT, history of revascularization or ablation for NSVT/VT, history of cancer, hemodialysis, echocardiographic parameters, simple electrocardiogram information, and laboratory data. For patient eligible for ICD indications, follow‐up items including laboratory data, echocardiographic and electrocardiographic parameters, NYHA classifications, Clinical Frailty Scale scores, and HF medications will also be collected again at 12 months after enrollment. For patients eligible for WCD indications, we will collect these follow‐up items at 3 months after enrollment, and again at 12 months thereafter. Simultaneously, we will monitor the observation items for at least 1 year, and until the final follow‐up period in cases followed up beyond 1 year, as in Tables 1 and 3. These include device introduction information, invasive treatments, and the occurrence of clinical events. After the observation period ending in December 2025, we will organize and analyze the data comprehensively by March 2026. Results of the study will be published in one or more peer‐reviewed journals by June 2026.

**TABLE 1 joa313028-tbl-0001:** Study schedule and main observation items.

Patient eligible for the indication of an ICD (including CRT‐D) Item(s) recorded		Registration	At 12 months after registration*	Final follow‐up
Patient information	Age, sex, height, weight, lifestyle habits, comorbidities, etc.	●		
	Electrocardiogram Echocardiogram	●	●	
	NYHA functional classification, Clinical Frailty Scale	●	●	
	Laboratory test results, medication information	●	●	
Observation items	Device implantation date (If not implanted, provide reason)			
	Invasive cardiac interventions			
	Clinical events (VT, VF, hospitalization for heart failure, cardiovascular death, etc.)			

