### Primary and secondary endpoints

2.4

The primary endpoint is the rate of cardiac implantable electronic device implementation. The secondary endpoints are shown in Table 4. Other significant factors besides the primary endpoint include the incidence of VT/VF, the presence of sudden death, all‐cause mortality, and HF hospitalization, as well as other variables. We will gather standard clinical background information, each patient's Clinical Frailty Scale score, laboratory test results (including measures of nutritional status), and serial changes, which will also serve as secondary endpoints.

**TABLE 4 joa313028-tbl-0004:** Primary and secondary endpoints.

Primary endpoint	
Rate of cardiac electronic device implantation (ICD, CRT‐D, WCD, CRT‐P, or None)	
Secondary endpoints	
Occurrence of any of the following	
1. VT/VF and Sudden death^a^	
2. Death from any cause	
3. Cardiovascular events (stroke/TIA or systemic embolism, myocardial infarction/unstable angina, cardiovascular death [including sudden cardiac death], hospitalization for heart failure, or other cardiovascular event requiring hospitalization)	
4. Stroke/TIA or systemic embolism	5. Myocardial infarction/unstable angina
6. Heart failure requiring hospitalization or other cardiovascular event requiring hospitalization	
7. Major bleeding (ISTH criteria^b^)	8. Clinically significant bleeding
9. Major bleeding or clinically significant bleeding	10. Cardiovascular death
11. Other causes of death	12. Device‐related complications
13. Invasive cardiac interventions (surgery, catheter‐based treatments, pacemaker implantation, etc.)	
14. If patients refused implantation, reasons for ICD/CRT‐D/WCD implantation refusal (1. Patient does not want risk associated with implantation, 2. Patient does not believe in benefit of ICD/CRT‐D/WCD, 3 Patient unable to pay for device, or 4 Other reasons)	
Change in the following from the time of enrollment to 1 year (WCD cases: at the time of WCD removal and 12 months after removal):	
1. NYHA (New York Heart Association) functional classification, Clinical Frailty Scale	
2. Echocardiographic measures	
3. Hemoglobin, hematocrit, creatinine, NT‐proBNP or BNP	
4. Nutritional status markers (serum albumin concentration, white blood cell count [peripheral blood lymphocyte count], total cholesterol, C‐reactive protein)	

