### Statistical analysis

2.6

Continuous variables will be presented as mean ± SD or median (25th, 75th percentile) values and categorical variables as the number (%) of patients. Between‐group differences in continuous variables will be analyzed by unpaired *t*‐test or Mann–Whitney U‐test, and between‐group differences in categorical variables will be analyzed by chi‐squared or Fisher's exact test. Serial changes in NYHA, Clinical Frailty Scale, Echocardiographic parameters, and biomarkers will be evaluated by paired *t*‐test. We will examine device introduction rates, especially focusing on the ICD (CRT‐D) implantation as primary prevention, and compare patient characteristics between the ICD/CRT‐D group and non‐ICD (no device/CRT‐P) group. We will investigate the distribution of reasons for ICD/CRT‐D/WCD implantation refusal. Patients eligible for a WCD indication, whether they are using a WCD or not, undergo evaluation for primary prevention ICD eligibility within the first 3 months after registration. If they meet the primary prevention ICD criteria at 3 months after registration, they are categorized as those eligible for ICD primary prevention indication. However, a subset of patients does not meet these criteria and is categorized as the “no ICD indication” group. We expect that most patients will fall into this “no ICD indication” group, and we will investigate and clarify the characteristics of these patients among those eligible for a WCD indication.

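### Change in LVEF is measured from an enrolment value capped at 35% by the entry rule and tested against zero, so regression to the mean alone can give a significant rise

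*Protocol article*

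**What the plan says.** **Entry (section 2.2).** The primary-prevention criterion is "NYHA class II or greater symptoms and an LVEF ≤35% despite optimal medical therapy". The summary sentence of that section applies the same LVEF and NYHA limits to the whole study: "aged 20 or older with LVEF ≤35% and NYHA class II or higher HF symptoms despite adequate medical therapy". The exclusions remove "severe HF patients classified as NYHA class IV", and the WCD criterion admits "HF symptoms of NYHA class II or III". LVEF is therefore cut on one side and NYHA on both.

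**Baseline (sections 2.3 and 2.4).** Patients already found eligible "will start enrollment in this study when informed consent regarding their medical condition and treatment options is obtained". Echocardiogram and NYHA class are recorded at registration (Table 1), and no separate reading after qualification is described. Table 4 lists as secondary endpoints "Change in the following from the time of enrollment to 1 year", covering NYHA, the Clinical Frailty Scale, echocardiographic measures, BNP or NT-proBNP and nutritional markers. WCD patients are measured at about 3 months and again 12 months later.

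**Test (section 2.6).** The only method named for these endpoints is "Serial changes in NYHA, Clinical Frailty Scale, Echocardiographic parameters, and biomarkers will be evaluated by paired" t-test. The sentence before it gives general between-group tests for continuous variables but does not link them to serial change. The limitations in the Discussion cover causality, confounding and a single ethnicity. They do not mention regression to the mean.

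**The concern.** A paired t-test asks whether mean change differs from zero. That null is sound only if zero is what one expects when nothing has truly changed. Here it is not. A measured LVEF is the patient's underlying level plus reading error and day-to-day variation, and a one-sided ceiling on the measured value enriches the cohort for readings that were low by chance. The next reading is higher on average with no recovery and no treatment effect.

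The WCD cohort has a further problem. Its registration values are taken soon after infarction, revascularisation or acute heart failure, and section 2.6 itself expects most of these patients no longer to meet the ICD criteria at 3 months. Improvement is expected before any data are seen, so rejecting zero change says little, and for LVEF the test cannot separate recovery from selection.

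At stake is a published secondary finding of improved LVEF, with a small p-value, that the entry rule could have produced unaided. The registry is meant to inform the choice of patients for devices.

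**Working it through.** The plan states no expected change, SD or power for these endpoints, so it has no figure of its own to reproduce. The target of 651 is a feasibility number built from device counts. It serves here only as an upper limit on the number of pairs, with 651/2 ≈ 325 for one half of the expected 50:50 split and 250 as an illustration of fewer complete pairs.

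**Inputs.** From the documents: the 35% threshold, the paired test and the 651. Assumed: mean and SD of LVEF in the population from which patients are drawn, reading error, normal distributions, no true change, two-sided 0.05.

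**1. Expected rise with no true change.** Let m be the source mean, S the total SD, r the test-retest correlation and z = (35 − m)/S. Then

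rise = (1 − r) × S × φ(z)/Φ(z).

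- *Mean 35, S 10, r 0.8.* z = 0 and φ/Φ = 0.3989/0.5 = 0.798, so the rise is 0.2 × 10 × 0.798 = 1.6 points.
- *Mean 38, true SD 9, error SD 5.* S = √(81 + 25) = 10.30, r = 81/106 = 0.764, z = −0.291 and φ/Φ = 0.3824/0.3854 = 0.992. The rise is 0.236 × 10.30 × 0.992 = 2.4 points. Simulation gives 2.41, with SD of change 6.8.

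| Assumed grid | Spurious rise in LVEF |
|---|---|
| Mean 35–42, true SD 7–9, error SD 3–6 | 0.76 to 5.22 points |
| Mean 30–40, total SD 8–12, r 0.6–0.95 | 0.2 to 5.2 points |

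**2. Rise that is already significant.** Smallest significant mean change = t(0.975, n − 1) × SD/√n. With SD of change 8:

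| Pairs | Standard error | Smallest significant rise |
|---|---|---|
| 250 | 0.51 | 1.00 |
| 325 | 0.44 | 0.87 |
| 651 | 0.31 | 0.62 |

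A rise of 2.41 points with 250 pairs gives t = 2.41/0.506 ≈ 4.8 from selection alone.

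**3. Probability of a significant rise with no true change.** The nominal value in that direction is 0.025. On the second grid it is 0.44–1.00 at n = 651, 0.25–1.00 at n = 325 and 0.10–1.00 at n = 100. In the case of mean 35, SD 10, r 0.8 (SD of change 6.1) it exceeds 0.99 at both n = 325 and n = 651, and is 0.73 at n = 100.

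**4. NYHA.** Simulation with no true change, 20–40% of readings one class out, and observed classes II–III enrolled. If the source population is 30% class I and 5% class IV, mean change is −0.08 to −0.15 classes and the probability of significance at n = 651 is 0.92–1.00. With 5% class I and 15% class IV the two cuts nearly cancel: mean change is about 0.00 and the probability 0.03–0.04.

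**5. The 3-month WCD value as a later baseline.** Three readings with no true change, mean 38, true SD 9, error SD 5, entry on the first reading. Change from the second to the third is about 0 in all patients. It is +1.5 points in those whose second reading is 35% or lower, and −4.0 points in those above 35%. The 3-month reading is clean for the whole cohort but not for subgroups defined by it.

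**The case against.** **NYHA.** A reader might infer that NYHA is bound to improve in the same way, since class I cannot enter but can be reached. The documents do not support that. Class IV cannot enter either, and step 4 shows that the result depends on an unknown class mix.

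**Biomarkers.** A reader might also put early falls in BNP and CRP, or a rise in albumin, down to regression to the mean. These are not entry criteria, and improvement after acute infarction or acute heart failure is mainly real recovery, which a change endpoint should capture. What remains is that zero is an uninformative null for the WCD cohort.

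**Causal claims and the second aim.** The plan does not attribute serial change to treatment, does not announce separate p-values by device status, and says in the Discussion that it cannot establish cause and effect. Nor does the paired test leave the second aim unserved: characteristics and clinical outcomes are compared by between-group tests, log-rank, Cox and propensity matching. All this stands. None of it makes zero the right null for LVEF.

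**Condensed article.** Baseline-adjusted models for secondary measures could sit in an analysis plan that is not shown. That would excuse silence. Here the article names the test, and the point concerns that choice.

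**Assumed inputs.** Every LVEF input beyond the threshold is assumed, and that the registration echocardiogram is the qualifying one is a strong inference, not a statement. At the low end (mean 30, SD 8, r 0.95) the rise is only 0.2 points and significance is far from certain. Both are fair and limit how firmly the size can be put.

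**Conclusion.** The point holds for LVEF. With a one-sided entry limit on the variable that is also the baseline, a paired test against zero has the wrong null. Under the assumed ranges, selection alone gives a rise of about 0.2 to 5 points, and about 0.6 to 1.0 points suffices for significance with 250 to 651 pairs at an SD of change of 8. A significant rise is therefore likely in central cases but not certain in all. This rests on assumed LVEF mean, spread and reliability, and on the enrolment reading being the qualifying one. A separate reading taken after qualification would largely remove the artefact.

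For NYHA the artefact is possible and of unknown size. For the biomarkers the matter is one of interpretation in the WCD cohort, not of selection.

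The change should be made, but it is not critical. These are secondary endpoints of an observational registry, and the device implantation rate and the event analyses are untouched.

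**What to change.** In section 2.6:

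1. Report within-group change in LVEF and NYHA as estimates with confidence intervals, without a p-value against zero, separately for the ICD-eligible and WCD-eligible cohorts. State that the change includes regression to the mean and, in the WCD cohort, expected early recovery.
2. If device groups are compared on change, model the 12-month value adjusted for the registration value and for the clinical covariates or propensity score already planned. Label the result as non-causal: device use is not randomised, CRT-D and CRT-P fall in opposite groups, and in the WCD cohort ICD eligibility depends on the 3-month result.
3. The 3-month value may serve as baseline for later change in the WCD cohort as a whole. It should not do so within the ICD-eligible and no-ICD-indication subgroups, which section 2.6 defines by that same 3-month assessment. Step 5 shows spurious changes of opposite sign there.

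The cost is a few sentences, slightly more analysis on data already being collected, and the loss of the within-group p-values.

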Patient eligible for the indication of a WCD Item(s) recorded		Registration	At 3 months (corresponding to the time of WCD removal phase)	At 12 months after WCD removal phase*	Final follow‐up
Patient information	Age, sex, height, weight, lifestyle habits, comorbidities, etc.	●			
	Electrocardiogram Echocardiogram	●	●	●	
	NYHA functional classification, Clinical Frailty Scale	●	●	●	
	Laboratory test results, medication information	●	●	●	
Observation items	Device implantation date (If not implanted, provide reason)				
	Invasive cardiac interventions				
	Clinical events (VT, VF, hospitalization for heart failure, cardiovascular death, etc.)				

* Allowable range: within 3 months.

Abbreviations: NYHA, New York Heart Association; VF, ventricular fibrillation; VT, ventricular fibrillation.

**TABLE 2 joa313028-tbl-0002:** Basical registration items (patient information).

(1) At registration

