NYHA functional classification (I / II / III / IV) Echocardiogram (LVEDV [mL], LVESV [mL], LVDd [mm], LVDs [mm], LAD [mm], LVEF [%], presence of moderate or severe valvular disease [MR, TR, AR, AS]) Electrocardiogram (heart rate, rhythm, QRS duration [ms], presence of ventricular pacing) Labotatory data (NTproBNP [pg/mL] or BNP [pg/mL], WBC [×10^9^/L], lymphocyte count [×10^9^/L], Hb [g/dL], Plt [×10^9^/L], BUN [mg/dL], Cr [mg/dL], eGFR [mL/min/1.73 m^2^], UA [mg/dL], AST [U/L], ALT [U/L], rGTP [U/L], Tcho [mg/dL], Na [mmol/L], K [mmol/L], TP [g/dL], Alb [g/dL], CRP [mg/dL])

Abbreviations: AR, aortic regurgitation; AS, aortic stenosis; Alb, albumin; ALT, alanine aminotransferase; AST, aspartate aminotransferase; BNP, brain natriuretic peptide; BUN, blood urea nitrogen; CRP, C‐reactive protein; Cr, creatinine; eGFR, estimated glomerular filtration rate; Hb, hemoglobin; LAD, left atrial diameter; LVDd, left ventricular diastolic diameter; LVDs, left ventricular systolic diameter; LVEF, left ventricular ejection fraction; LVEDV, left ventricular end‐diastolic volume; LVESV, left ventricular end‐systolic volume; end‐systolic volume; MR, mitral regurgitation; NT‐proBNP, N‐terminal pro‐brain natriuretic peptide; NSVT, Non‐sustained ventricular tachycardia; NYHA, New York Heart Association; Plt, platelet; rGTP, γ‐glutamyltranspeptidase; Tcho, total cholesterol; TP, total protein; TR, tricuspid regurgitation; UA, uric acid; VT, ventricular tachycardia; WBC, white cell count.

**TABLE 3 joa313028-tbl-0003:** Observation items.

Observation Items (To be observed for a minimum of 12 months from the date of registration)

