Clinical events, such as VT/VF and sudden death, and cardiovascular events, for each group will be reported as percentages of the total population and annual frequencies per person‐year. Additionally, we will utilize the Kaplan–Meier method to calculate the cumulative event rates of clinical events, particularly focusing on VT/VF and sudden death, in the ICD/CRT‐D group, the non‐ICD (no device/CRT‐P) group among patients eligible for primary prevention, and compared these two groups using the log‐rank test. We will conduct Cox proportional hazards analysis to estimate hazard ratios (HRs) and 95% confidence intervals (CIs) for factors related to clinical events. Since the cardiovascular event rate is expected to provide sufficient data for multivariate analysis, we will conduct multivariate analysis to calculate the HR and 95% CI of the non‐ICD (no device/CRT‐P) group relative to the ICD/CRT‐D group in primary prevention for cardiovascular events by adjusting for clinically relevant factors. Based on the HINODE study, the annual occurrence rate of appropriate therapy for VT/VF with heart devices was approximately 6%. The all‐cause mortality rate for the group that did not have an ICD implanted (non‐device and pacing cohorts) was in the range of 8% (over the entire observation period).^17^ In the MADIT‐RIT Trial, the rate of appropriate ICD operation was also above 6%.^24^ In the MADIT II Trial, the rate of sudden cardiac death was approximately 10% in the non‐ICD group and less than 4% in the implanted ICD group, respectively.^15^, ^25^ Considering the low incidence of VT/VF and sudden death in primary prevention (approximately 5%–10%), the limited number of events may render multivariate Cox proportional hazards analysis impractical. Therefore, the propensity score model will be developed using selected variables according to clinical relevance. We will again draw the Kaplan–Meier method along with HR and 95% CI for VT/VF and sudden death for the propensity matched non‐ICD patient group compared with the propensity matched ICD patient group in primary prevention. As such, the results of elected patients after propensity score matching, along with all cohorts, along will be presented in the main text. For other groups, like those eligible for secondary prevention ICD and WCD, we plan to conduct the most comprehensive adjustment analysis possible, considering that the adjustable variables may change with the increasing number of cases.

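### WCD patients reclassified at 3 months enter the primary-prevention analyses with no time zero of their own; counting from registration would credit them with up to 3 months of immortal time for death and, in effect, sustained VT/VF

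*Protocol article*

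**What the plan says.** Section 2.6 (Statistical analysis) evaluates patients registered under the WCD criteria for a primary-prevention ICD indication during the first 3 months and then regroups them: "If they meet the primary prevention ICD criteria at 3 months after registration, they are categorized as those eligible for ICD primary prevention indication". The others form a group without ICD indication, which the authors expect to be the majority.

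The start of observation appears in the heading of Table 3: "To be observed for a minimum of 12 months from the date of registration". Section 2.3 (Study schedule) adds "we will monitor the observation items for at least 1 year" and gives reclassified patients no different start. It schedules the WCD group's assessments "at 3 months after enrollment, and again at 12 months thereafter", and Table 1 labels the later one "At 12 months after WCD removal phase".

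In section 2.6, clinical events for each group "will be reported as percentages of the total population and annual frequencies per person‐year". The Kaplan-Meier and log-rank comparison of ICD/CRT-D with no device/CRT-P is made "among patients eligible for primary prevention". The adjusted Cox comparison for cardiovascular events and the propensity-matched comparison for VT/VF and sudden death are also confined to primary prevention. No time zero, landmark or delayed-entry rule is stated for any of them.

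**The concern.** A WCD patient joins the primary-prevention group only by reaching the 3-month assessment and qualifying there. A patient who dies before it cannot join. One who has VF or sustained VT without a reversible cause before it fits the secondary-prevention criteria in section 2.2. Patients registered directly under the primary-prevention criteria face no such hurdle, and their early deaths and arrhythmias count.

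If both kinds of patient are timed from registration, the reclassified patients add person-time to the denominator during which the selected events could not have entered the numerator. Rates of these events are then too low and Kaplan-Meier curves too favourable in the early months. VT/VF with sudden death, the outcome that section 2.6 singles out, is among those most exposed. In the same months some of these patients may be wearing a WCD, a state that belongs to neither comparison group.

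**Working it through.** There is no stated figure to reproduce: the 651 patients are a feasibility target without alpha, power or effect size, and this point does not depend on them.

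**Inputs**
- Annual rate r = 0.06: the approximate rate of appropriate device therapy that section 2.6 takes from the HINODE study, used here as a stand-in for the rate of the selected events and assumed constant.
- Immortal time: 0.25 year (section 2.6), taken at its maximum.
- Follow-up T from registration: 1.0 year (stated minimum) to 2.75 years (1 April 2023 to 31 December 2025, section 2.1). The midpoint is (1.0 + 2.75)/2 ≈ 1.9 years.
- Share of converters in each arm: not given. The shares below are assumptions.

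**Reclassified patients alone, timed from registration**

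Events per patient: E = 1 − exp(−r(T − 0.25)). Person-years per patient: 0.25 + E/r. Apparent rate = E / (0.25 + E/r).

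| T (years) | E | Person-years | Apparent rate per year | Relative to 6% |
|---|---|---|---|---|
| 1.0 | 0.0440 | 0.9834 | 4.5% | 0.75 |
| 1.75 | 0.0861 | 1.6845 | 5.1% | 0.85 |
| 2.75 | 0.1393 | 2.5715 | 5.4% | 0.90 |

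Starting the clock at 3 months removes the 0.25 from the denominator and gives E/(E/r) = r = 6.0%.

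At 5% or 10% per year the relative figures hardly change: 0.75 and 0.74 at 1 year, 0.90 and 0.90 at 2.75 years.

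**A whole arm with converter share f**

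With D = 1 − exp(−rT) for direct entrants, apparent rate = [fE + (1 − f)D] / [f(0.25 + E/r) + (1 − f)D/r].

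For f between 10% and 30%, a true 6% appears as 5.85% to 5.54% at T = 1 and as 5.94% to 5.82% at T = 2.75.

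**Ratio non-ICD/ICD when the true ratio is 1**

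| Converter share, ICD arm / non-ICD arm (assumed) | T = 1 | T = 1.9 | T = 2.75 |
|---|---|---|---|
| Equal shares | 1.00 | 1.00 | 1.00 |
| 30% / 10% | 1.06 | 1.03 | 1.02 |
| 40% / 10% | 1.09 | 1.04 | 1.03 |

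For example, 40%/10% at T = 1.9 gives 5.92% / 5.67% = 1.04. Reversing the shares reverses the direction (10%/30% gives 0.95 at T = 1 and 0.98 at T = 2.75).

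**The case against.** The best defence is that section 2.6 never says the survival clock starts at registration. The Table 3 heading sets a minimum period of data collection, the WCD group has its own visits at 3 months and 12 months after that, and a journal article may leave the time origin to the full protocol or the SAP. This stands in part: the bias is conditional on counting from registration. But the article itself sets out the regrouping rule, the groups compared and one start of observation. Followed as written, these produce the problem. The later visits are data-collection points and do not define an origin.

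Three stronger readings are tempting, and the documents do not support them.

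- *The 3 months are free of all events.* They are not. Heart failure hospitalization, stroke, myocardial infarction and bleeding do not prevent reclassification. VT is recorded from five beats (Table 3), and NSVT does not bar primary-prevention eligibility (section 2.2). The cardiovascular composite used for the multivariable Cox model is therefore only partly affected. The exclusion of sustained VT/VF is itself an inference from the eligibility criteria; no explicit rule transfers such patients to secondary prevention.
- *Early events are lost to the study.* Those patients stay in the registry and can be reported in the WCD group. They are missing only from the primary-prevention group.
- *The hazard ratio is necessarily biased.* With equal converter shares it is not.

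Scale also matters. If all 651 patients were in the primary-prevention comparison, split 1:1 (a generous assumption), 6% per year over 1.9 years would give 651 × (1 − exp(−0.114)) ≈ 70 events. The 95% half-width for the log hazard ratio would be about 1.96 × 2/√70 ≈ 0.47, against a shift of ln(1.04) ≈ 0.04. The distortion of the comparison is small beside its imprecision. The understatement of absolute rates, however, needs no imbalance between arms.

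**Conclusion.** The point holds in a limited form. Membership of the primary-prevention group is decided for some patients up to 3 months after the only start of observation the article gives, and nothing aligns the two. Timed from registration, reclassified patients carry immortal time for death, sudden death and, in effect, sustained VT/VF. The rate of these events among them is understated by about a quarter at 1 year of follow-up and about a tenth at 2.75 years.

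At group level the effect is modest, since converters are expected to be a minority of WCD patients. The effect on the ICD versus non-ICD ratio ranges from none to 8-9% over the shares tabulated. These sizes rest on a constant 6% annual hazard, a full 3 months of immortal time and assumed converter shares. The article gives no number of converters, so the actual size cannot be computed. It merits correction before analysis because the remedy is simple and absolute event rates in primary prevention are a planned result.

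**What to change.** Add to section 2.6 that, in the primary-prevention person-year, Kaplan-Meier, Cox and propensity-matched analyses, time zero is registration for patients who enter directly and the 3-month eligibility assessment for reclassified WCD patients (or that the latter enter the risk set late, at that date). Report months 0-3 of WCD-indication patients in the WCD-group analysis, including those who die or have sustained VT/VF before the assessment.

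For reclassified patients, use the 3-month values of covariates collected again at that visit and registration values for the rest, such as comorbidities. Table 1 lists ECG, echocardiogram, NYHA class, frailty, laboratory tests and medication at 3 months. The follow-up part of Table 2 does not list frailty or medication and should be brought into line.

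The cost is analysis wording and up to 3 months less person-time per converter. A patient registered on 31 December 2024 and followed to 31 December 2025 would have only about 9 months from the new origin, so a 1-year estimate must treat such patients as censored.
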